**Secondary endpoints:**

● Linking changes in the inflammatory profile in adipose tissue and systemic level with clinical and biological changes (including insulin sensitivity).

# Selection of subjects

## Study population:

### Duration of the participation of the people in the research:

The total duration of participation of each subject will be 12 consecutive weeks.

### Description of the participating subjects:

Inclusion Criteria

1 . BMI 27-38 kg/m2
2 . Subjects aged from 25 to 65 years. Postmenopausal for at least 6 months.
3 . Subject has given his consent to participate by writing
4 . Non-diabetic subjects
5 . Fasting blood glucose less than 1.26 g / l

### Exclusion Criteria:

SGOT or SGPT greater than 2.5x the normal value
• High blood glucose:1.26 g / l
• Known heart failure (stage 2 or 3) or confirmed by echocardiography (ejection fraction <60 %) if history of coronary artery disease
• Hepatic impairment known
• Chronic liver disease
• Renal impairment: clearance < 60ml/mn
• Anemia: Hb < 10g/dl
• Participation in another study
• Processing corticosteroids
• Inflammatory Disease
• Any illness making the execution of the protocol or interpretation of results difficult
• Taking antibiotics in the previous 3 months

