These results from animal studies were completed by two independent human studies. Comparison of the microbiota composition between lean and obese humans and its evolution in obese patients loosing weight during a low calories or low fat intervention indicated a lesser proportion of Bacteroidetes and increased Firmicutes in obese subjects that tended to revert to that of lean controls upon low calory dietary intervention [Ley et al 2006]. Dynamics of microbiota composition and bacterial fermentation products in obese patients upon low calory intervention showed a reduced concentration of butyrate and lesser proportions of the *Roseburia*-*Eubacterium rectale* subgroup (Phylum Firmicutes) and

*Bifidobacterium* genus as obese patients were losing weight [Duncan et al 2007]..

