# ObjectiVEs

**MICRO-Obes** aims to characterize the relationship between intestinal microbiota and the nutritional, inflammatory and metabolic status of the host before and after calorie restriction of 1200 Kcal for 6 weeks followed by a stabilization phase 6 weeks among obese.

**1. A nutritional and metabolic approach will be conducted to assess:** 1) weight loss, 2) reduction of fat mass and adipocyte size, 3) markers of systemic inflammation (CRP-us, IL 6, SAA), 4) plasma lipids, plasma glucose and insulin, 5) the insulin sensitivity, 6) changes in gene and protein expression in adipose tissue (500 mg by suction under local anesthesia with a fine needle) of inflammation factors characteristic of adipocytes and macrophage infiltration.

**2. A metagenomic approach** will also be implemented in order to sequence the dominant genetic repertoire of human intestinal microbiota (stool samples) and identify the functions of the relevant host-microbiota dialogue in capturing energy from food.

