**Justifications for the selection of a restriction to 1200 kcal for 6 weeks:**

Weight loss by "only" dieting is significant when energy intake is typically significantly lower than energy expenditure. In this study, it will be recommended for subjects to continue their usual level of physical activity. Schemes commonly used in the clinic or in clinical investigation programs are threefold: very low calorie diet (VLCD or very low calorie diet <800 kcal, intermediate (LCD or low calorie diet 800-1500 kcal per day) or very moderate (500 kcal less than usual intakes). Such approaches to the medical management of obesity have been the subject of a recent review in the New England Journal of Medicine (11).

The choice of intermediate diet and duration is based on several arguments: 1) the absence of " risk " associated with a very low calorie diet (VLCD) requiring special monitoring including vitamins and potassium, 2) induction of a slope of rapid weight loss: in previous programs in the team (Project: Effect of two different hypocaloric diets on weight loss and on inflammatory markers) and European programs (**NUGENOB and DIOGENES**), we were able to evaluate this aspect, in agreement with other teams, as weight loss is induced faster in this type of low calorie diet compared with the moderate diet and becomes significant at around 5-6 weeks (eg Figure 1), 3) the feasibility of these programs: these " low calorie diets" were used repeatedly by our team ( Project of [name]: Effect of two different hypocaloric diets on weight loss and on inflammatory markers) and are well tolerated by the subjects that are regularly monitored by the dietitian in accordance with the recommendations, 4) the observation of a transition of the bacterial flora switch firmicute / bacteroides observed at the limit of significance in a pilot study by our collaborator ANR ([name]).

Therefore we selected a six week diet as the point where even the poor responders monitored under a European project lost about 6% of their initial weight. This is consistent with the work of Gordon Group (12).

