## Recruitment and output test

**Recruitment of participants:**

The subjects will be recruited by public advertisement.

**Exit (drop-out) protocol:**Deliberate decision of a person:
The exit from the study protocol is possible at any time if requested by the participant. More specifically, if participants do not wish to continue the tests, they need only to report to the examiner.

**Decision imposed:**Participants who cannot perform the tasks related to research will be excluded from the protocol.

**Expected Benefits and / or foreseeable risks to persons**No specific individual results are expected from the study. In the exceptional case where, for a given individual, the study would highlight a health risk, relevant data are communicated to the occupational physician who can communicate the most relevant information to the individual case, in the context of respect for persons and medical confidentiality.

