**Constraints of the test.**

The regulation of clinical trials in humans, has forbidden participation in two contradictory experiments simultaneously. If the subject agrees to participate in this study, they should not participate in another trial with diets or drugs during the same period.

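### Nothing in the eligibility criteria screens out recent dieting or weight change, so day 0 need not be a stable pre-restriction baseline in this uncontrolled before/after study

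*Protocol*

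**What the plan says.** The Inclusion Criteria set BMI (27 to 38), age with menopausal status, consent, non-diabetic status and fasting glucose. The Exclusion Criteria cover liver, heart and kidney function, glucose, anaemia, corticosteroids and inflammatory disease, plus three items that bear on this point:

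- "Taking antibiotics in the previous 3 months", the only item with a look-back period;
- "Participation in another study", with no time window;
- "Any illness making the execution of the protocol or interpretation of results difficult", a general clause limited to illness.

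Under Constraints of the test, subjects are told that "they should not participate in another trial with diets or drugs during the same period". The Overview table has eligibility checked at V1 (day -14 to -1) and again at V2 (day 0). The experimental design section asks for a one-week food diary at the start and end of each diet period.

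The Objectives compare status "before and after calorie restriction of 1200 Kcal for 6 weeks" and a stabilisation phase. The main criteria include weight and fat loss, the F/B change and systemic inflammation. There is one cohort of 50, and "The subjects will be recruited by public advertisement".

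**The concern.** The study asks what calorie restriction does to the microbiota and the host. It has no control arm, so each subject's day-0 value is the only reference. The protocol itself gives two reasons to think that prior dieting could move that reference. Section 1.1 reports that the F/B balance "tended to revert to that of lean controls upon low calory dietary intervention". The justification of the stabilisation phase describes mechanisms that drive weight back up once restriction ends.

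A volunteer several weeks into a commercial diet, or regaining after one, meets every listed criterion if otherwise suitable. For that person the day-0 stool, biopsy, weight and inflammatory markers do not describe a stable state before restriction. The antibiotic exclusion shows that a look-back was thought necessary to protect the stool baseline; no such look-back covers the exposure under study. Eligibility is fixed in the protocol, so a statistical analysis plan cannot supply the missing criterion.

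**Working it through.** **1. Does any clause close the gap?**

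| Provision | Current diet trial | Diet study ended before V1 | Self-directed or commercial diet | Recent weight change |
|---|---|---|---|---|
| Other-study exclusion | excluded | no look-back stated | not covered | not covered |
| Constraints of the test | excluded | same period only | not covered | not covered |
| General clause | illness only | illness only | illness only | illness only |
| Food diary | recorded | missed | recorded if current | not covered |

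No entry rule is tied to the diary, and no weight-stable run-in is described between V1 and V2. V1 may fall as late as the day before V2.

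**2. How fast does the protocol expect change?** The description of procedures schedules blood and a biopsy after 7 days to look at early changes in weight and in adipose-tissue inflammation. A volunteer already dieting for weeks at V2 is past that point.

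**3. The plan's own sample-size figure.** The section on the number of people to include gives a change of at least 40%, standard deviation 16, alpha 0.05, beta 0.10 and N = 50. On one common scale, for a paired change, two-sided:

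n = [SD × (z₀.₉₇₅ + z₀.₉₀) / δ]² = [16 × (1.960 + 1.282) / 40]² = 1.68, so 2 (5 by the exact paired t).

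The stated 50 is not reproduced. That is a separate matter. It means that the power figures in step 5 must be calibrated to N = 50 rather than taken from 40 and 16.

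**4. Dilution of the mean change (illustration).** Assume that a fraction p of subjects has already undergone half of the expected change before day 0:

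mean change = 40% × (1 − p/2)

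- p = 10%: 40 × 0.95 = 38%
- p = 30%: 40 × 0.85 = 34%

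Both p and the half are assumptions.

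**5. Power (illustration).** Assume that N = 50 gives exactly 90% power for the intended change and that the SD is unchanged. The intended standardised change is then 3.242/√50 = 0.458, and power = Φ(3.242 × r − 1.960), where r is the retained share of the mean change.

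| p | Half already shifted: r | Power | Fully shifted: r | Power |
|---|---|---|---|---|
| 10% | 0.95 | 87% | 0.90 | 83% |
| 30% | 0.85 | 79% | 0.70 | 62% |

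Taken at face value, the stated 40 and 16 leave power near 100% in 50 subjects even for a change of 34. On those inputs the issue is bias in the estimate, not loss of power.

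**The case against.** The strongest reply is that several safeguards exist and the evidence for harm is thin.

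- **Diet-study participants.** A reader might infer that someone who left a diet study the day before V2 is eligible. The protocol does not support that: other-study participation is an exclusion, and eligibility is checked at V1 as well as V2, so such a person would normally fail at V1. What remains open is a diet study that ended before V1, and any diet outside a study.
- **The diary.** A reader might infer that prior dieting could never be separated from the study diet's effect. That is too absolute: a subject restricting at baseline may show in the diary and can be examined separately. A diet that has ended would not show.
- **The F/B evidence.** A reader might take the protocol as having established that restriction shifts F/B. It is more guarded: the published proportions only tended to revert, and the pilot switch was "firmicute / bacteroides observed at the limit of significance in a pilot study". Still, the choice of diet and the sample size both rely on that shift.
- **Meaning of before.** The objective refers to the 1200 kcal study diet, and day 0 precedes that diet for everyone. That is literally right, but it does not make day 0 a stable state before any restriction.
- **Recruitment.** It is tempting to infer that public advertisement attracts people already dieting. That is plausible, but nothing in the protocol shows it.
- **Direction and size.** Current dieting and regain may act in opposite directions, and no prevalence is given. This stands in full: no net bias can be derived from the document.

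**Conclusion.** The gap is real but limited. Self-directed or commercial restriction, recent weight change, and a diet study ended before V1 are all compatible with entry, and no other clause covers them. For such subjects day 0 is not a stable pre-restriction baseline, and the design has no second comparator. Current restriction would most likely make the measured change in F/B, weight, fat mass and inflammation too small; regain could push it the other way.

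The size is unknown. The fall from 40% to between 38% and 34% rests on an assumed 10% to 30% of subjects having had half of the change already. The power figures rest further on N = 50 being exactly right for 90% and on an unchanged SD. The protocol contains no outright contradiction here. This is an inexpensive improvement to eligibility, and should be rated as that.

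**What to change.** Add one exclusion criterion: *calorie-restricted diet, participation in a diet study, or self-reported weight change above a pre-set threshold in the previous 3 months*. A threshold of 3 kg is one example; the protocol offers no basis for a particular value, so the sponsor should confirm it. The three-month window matches the one already used for antibiotics, for consistency and not because the protocol shows that diet effects last that long.

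Record weight history and recent dieting at V1. Give the Constraints of the test paragraph the same look-back for diet studies, so that it agrees with the new criterion.

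The cost is one criterion and a short set of screening questions, some extra screen failures within the 8-month recruitment period, and reliance on self-report.

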### Number of people to include:

Effective Calculation: 50 subjects are required to show a change in the ratio of microbiota Firmicutes / Bacteroidetes of at least 40% and a standard deviation of 16 by setting the risk to   0.05 and the risk to 0.10 (calculations made after the results of a pilot study with a low calorie diet of 1200 Kcal).

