## Category of research :

## Physiopathological study

## Presentation of the experimental design (CF Schéma général : page 2)

A population of 50 obese subjects will be selected after a review of pre inclusion.

After inclusion, subjects follow a low calorie diet of 1200 Kcals for 6 weeks followed by a stabilization phase of 6 weeks. The low calorie diet will be provided and delivered by the laboratory CEPRODI-KOT (attached a list of products offered and a standard menu with products CEPRODI-KOT). Dietary advice will be given at the beginning of each period, patients will be contacted in the middle of each period and a dietician will always contactable by phone or email. The dietician will contact the patient by phone once a week to ensure that there are no difficulties. Data collection will be done at the beginning and end of each period using a food diary kept for one week. The food composition (nutrients) is obtained using a French food composition table.

The stabilization phase of weight will be adjusted depending to the resting energy expenditure (REE) of each patient and will be calculated by the dietician according to the formula of Harris and Benedict :
REE man = 66.473 + (5.003 x height in cm ) + (13.752 x weight in kg) - (6.755 x age)
REE Woman = 655.096 + (1.850 x height in cm ) + (9.563 x weight in kg ) - (4.676 x age)

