## Flow-Chart

- Recruitment period: 8 months.

In case of study withdrawal due to recurring medical problems, the withdrawn subject will not be replaced.

- Total study duration: 24 months.
- The total duration of participation for each subject will be 12 consecutive weeks.

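### The 50 subjects said to give 90% power do not follow from the stated 40% change and SD of 16, because the SD's unit and type and the baseline ratio are missing

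*Protocol*

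**What the plan says.** The calculation is in the Protocol under Number of people to include. It states that "50 subjects are required to show a change in the ratio of microbiota Firmicutes / Bacteroidetes" and gives as inputs "a change in the ratio of microbiota Firmicutes / Bacteroidetes of at least 40% and a standard deviation of 16", with the two risks set at "0.05 and the risk to 0.10". The Greek symbols are missing from the text at hand; I read the risks as alpha and beta, so power is 90%. The inputs are attributed to a pilot study of a 1200 kcal diet. The 40 carries a percent sign and the 16 carries no unit. The baseline ratio, the test, its sidedness and the kind of SD (of the paired change, or between subjects at one visit) are not given.

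The design is a single group measured before and after the diet (Objectives; Presentation of the experimental design). The latter section also says "A population of 50 obese subjects will be selected after a review of pre inclusion", so the number required and the number selected are the same. The Flow-Chart section says that after withdrawal for recurring medical problems "the withdrawn subject will not be replaced".

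**The concern.** The change in the Firmicutes/Bacteroidetes ratio is one of six main criteria and the only one used to size the trial. Read as printed, 40 against an SD of 16 is a very large standardised effect, for which a before/after comparison needs only a handful of subjects. Either the SD is not what it appears to be, or the 50 was obtained some other way.

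The consequence is that nobody can check the 90% power claim or say what change 50 subjects can detect. The answer could be a few percentage points or the full 40. The participants undergo repeated adipose tissue biopsies in research that the protocol describes as bringing them no benefit, so the number exposed should rest on a calculation that reproduces.

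**Working it through.** **Inputs.** From Number of people to include: change 40%, SD 16, alpha 0.05, beta 0.10, N = 50. From Objectives: one group, paired before/after. Sidedness is not stated. I take two-sided as the main case and also show one-sided.

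**Step 1. Try to reproduce 50 with 40 and 16 on one percent scale.**

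- Standardised effect: d = 40/16 = 2.5.
- Normal approximation: n = ((1.960 + 1.282)/2.5)² = 1.68, so 2 subjects.
- Exact paired t-test (noncentral t, n − 1 degrees of freedom, noncentrality 2.5√n): n = 4 gives 89.9% power and n = 5 gives 98.2%. The requirement is 5. One-sided it is 4.
- Power at n = 50 exceeds 99.9%.

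**Step 2. Try other same-scale readings.**

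| Reading | N needed (two-sided unless noted) |
|---|---|
| 16 is a per-visit SD, correlation 0.8 (SD of change 10.1) | 3 |
| Per-visit SD, correlation 0.5 (SD of change 16) | 5 |
| Per-visit SD, correlation 0 (SD of change 22.6) | 6 |
| Per-visit SD, correlation −1 (SD of change 32) | 9 |
| Alpha and beta exchanged (0.10 and 95% power) | 4 |
| Two independent groups, normal approximation | 4 per group |

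The SD of change here is 16√(2(1 − correlation)). None of these comes near 50. Inflating 5 to about 50 for dropout would need about 90% dropout: 5/(1 − 0.9) = 50.

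**Step 3. Solve for what would make 50 right.**

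With n = 50, 90% power and a two-sided 5% paired t-test, the detectable standardised change is d = 0.4677.

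- With a change of 40 points, the SD of the paired change must be 40/0.4677 = 85.5 percentage points.
- With SD 16 in units of the ratio, the detectable change is 0.4677 × 16 = 7.48 units. If that is 40% of baseline, the baseline ratio is 7.48/0.40 = 18.7.

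The normal approximation gives 87.3 percentage points and a ratio of 18.3. None of these values appears in the protocol.

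**Step 4. See how far N depends on the missing baseline ratio (SD 16 in ratio units, exact t).**

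| Baseline ratio (assumed) | 40% change | N needed |
|---|---|---|
| 10 | 4 | 171 |
| 15 | 6 | 77 |
| 18.7 | 7.48 | about 50 |
| 20 | 8 | 44 |
| 30 | 12 | 21 |

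**Step 5. Effect of having no dropout margin.** This applies only if 50 is truly the 90%-power number, so that d = 0.4677. The protocol gives no dropout rate, so the evaluable numbers are my assumption: 45 evaluable give 86.6% power and 40 give 82.2%. To keep 90%, the detectable change rises from 0.47 SD to 0.49 SD at 45 and 0.53 SD at 40. On the percent reading of Step 1, losses of this order would not matter.

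**The case against.** The best defence is that the 16 has no unit. The ratio is dimensionless, so an SD in ratio units is a legitimate reading, and on that reading 50 is correct at a baseline ratio near 18.7. The text is also a translation with its symbols lost. This stands, and it limits the point: a reader might infer that the trial needs 5 subjects and is ten times too large, but that holds only if the SD is a percentage, which the protocol does not say. The defence does not rescue the sentence, however, because the baseline ratio on which it depends is not given.

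Four further inferences are tempting, and the document does not support them.

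- **That a null result would be uninterpretable.** On the percent reading power at 50 exceeds 99.9%, and a null result would be highly informative.
- **That the pilot had only about 3 subjects.** The section justifying the 1200 kcal restriction reports a "bacterial flora switch firmicute / bacteroides observed at the limit of significance in a pilot study". An effect of 2.5 SD would be borderline at n = 3 (t = 2.5√3 = 4.33 against a critical value of 4.30). But the protocol does not say that this is the pilot behind the sample size, and an observed pilot effect need not equal the planning effect.
- **That fewer than 50 will be evaluable.** The no-replacement rule covers withdrawal for recurring medical problems only, and no dropout rate is given. A missing allowance is not a predicted loss.
- **That no extra enrolment is needed.** At a baseline ratio of 10, in ratio units, the requirement would be 171.

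**Conclusion.** The point holds in this form: the stated 50 and its 90% power cannot be obtained from the stated inputs. With both figures in percent, the requirement is 5 and 50 is about ten times that. With the SD in ratio units, the requirement is indeterminate, running from 171 to 21 as the assumed baseline ratio goes from 10 to 30. The detectable change at 50 evaluable subjects is 0.47 SD of the within-subject change. That is 7.5 points if the SD is 16 percentage points, or 40 points if it is 85.5.

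These results assume a paired t-test at two-sided 5%; a one-sided test does not bring the percent reading near 50. The protocol chose to fix this calculation with numbers, so it is not a detail left for an analysis plan. Whether the trial is over-sized, correctly sized or under-sized for a 40% change cannot be settled from the document. The absence of a dropout allowance is a secondary matter, relevant only if 50 is the true 90%-power number.

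**What to change.** Correct the paragraph under Number of people to include from the pilot data. Give the baseline ratio, the SD of the within-subject change with its unit, the test and its sidedness, and the number expected to be evaluable. Then restate whatever N or power results.

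If the pilot inputs cannot be recovered, remove the 40% and 16 and state what the chosen size delivers. Suggested wording: *With 50 evaluable subjects, a two-sided 5% paired t-test has 90% power to detect a mean change of 0.47 SD of the within-subject change in the Firmicutes/Bacteroidetes ratio (0.49 SD with 45 evaluable, 0.53 SD with 40).* Analysing the ratio on the log scale is optional; if it is used, the SD should be on that scale too.

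The rewording costs one paragraph. Whether the number enrolled should change can be judged only once the inputs are recovered. The fallback wording has its own price: the protocol would no longer claim power for a 40% change.
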